**Table 1 Tab1:**
[figure not shown]
Timeline and applied tests

**Fig. 1 Fig1:**
[figure not shown]
Participant flow diagram according to the Consolidated Standards of Reporting Trials (CONSORT) 2010 statement

**Fig. 2 Fig2:**
[figure not shown]
Trial procedure flow sheet

### Sample size {14}

Since our study is the first in its kind, we calculate the sample size base on CRP as one the most important parameters of this study. Based on a previous study using selenium supplementation on patients with inflammation to reduce inflammatory factors such as CRP [42], and considering 80% power, and the first type error α = 0.05 and the second type error β = 0.20, based on following equation sample size were calculated:$$n\hspace{0.17em}=\hspace{0.17em}2[{(\mathrm{Z}1-\mathrm{\alpha }/2\hspace{0.17em}+\hspace{0.17em}\mathrm{Z}1-\upbeta )}^{2}\hspace{0.17em}\times \hspace{0.17em}{\mathrm{S}}^{2}]/{\Delta }^{2}\hspace{0.17em}\to \hspace{0.17em}2[{(1.96\hspace{0.17em}+\hspace{0.17em}0.84)}^{2}\hspace{0.17em}\times \hspace{0.17em}{(10.9)}^{2}]/{(8)}^{2}$$

A total of 60 subjects (i.e., 30 participants in each group) would be required.

### Recruitment {15}

Patients will be selected according to the entry and exit criteria from the patients who refer to Seyyed al-Shohada Center, an academic center for referral of patients to receive iodine, Isfahan, Iran.

## Assignment of interventions: allocation

### Sequence generation {16a}

After meeting the entry criteria, each patient will be randomly assigned to one of the two supplemental groups with selenium or placebo using the reliable random number generator website “https://www.sealedenvelope.com/simple-randomiser/v1/lists” and using a block size of four based on age and sex using the website https://www.sealedenvelope.com/simple-randomiser/v1/lists, with the ratio of 1:1. Sample patients will be 20 to 65 years old. Therefore, the age threshold of 20 to 65 years will be considered. For the randomization, the stratification factors are age (20 to 45, or 46 to 65) and sex (male or female).

### Concealment mechanism {16b}

Completely identical packages of selenium and placebo tablets with blinded labels A or B will be provided to the researcher without specifying the type of supplement. Researchers and patients will not know the type of supplement on each label until the end of the statistical analysis.

### Implementation {16c}

An independent reviewer will assign the participants to the intervention or control group, and also the generation of the allocation sequence of the patients will be monitored by the second researcher ([name]).

## Assignment of interventions: blinding

### People who will be blind {17a}

This will be a double-blind study, so the researchers and the subjects will not know which group they will enter. Also, selenium and placebo supplements will be produced in the same way in terms of shape, color, size, and smell, and they will have the same packaging.

### Procedure for unblinding if needed {17b}

The disclosure of the label of the supplements will only take place at the end of the study after the completion of the statistical analysis. In case of any unblinding during the study, it will be reported in detail in the Iranian Registry of Clinical Trials and the final results of the study.

## Data collection and management

### Plans for assessment and collection of outcomes {18a}

Major salivary glands (echogenicity, size, margin, and contour) will be examined by sonography before and 6 months after the 10-day intervention with selenium or placebo.

A questionnaire evaluating the degree of dry mouth and its effects on the daily life of patients will be used to evaluate the sense of taste and secretion of salivary glands.

### Plans to promote participant retention and complete follow-up {18b}

To encourage patients to cooperate as much as possible, it will be explained about the possible effects of selenium supplementation on the reduction of complications caused by the treatment of thyroid cancer patients with radioactive iodine.

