## Interventions

### Explanation for the choice of comparators {6b}

While receiving standard treatment, patients will be placed in one of two groups receiving a selenium supplement or placebo. The treatment group will receive one selenium capsule containing 200 µg of selenium per day and the control group will receive one placebo capsule containing 200 µg of maltodextrin per day for 10 days (3 days before to 6 days after radioactive iodine treatment).

The reason for choosing 200 µg is that a dosage of 200 µg/day per extra-dietary supplementation of selenium is generally considered safe and adequate for an adult of average weight [39]. In addition, the supplements available in the Iranian market have a dose of 200 μg per tablet. Also, Lee et al.’s study [38], which is somewhat similar to our study, used a dose of 300 μg. Therefore, 200 μg is close to this dose.

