### Relevant concomitant care permitted or prohibited during the trial {11d}

The patient will receive all the usual care and treatment under the supervision of a specialist doctor. There will be no change in receiving standard care during the study. Patients only received selenium supplements or a placebo in addition to receiving routine treatments.

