### Provisions for post-trial care {30}

All standard treatments will be continued after the study, but selenium or placebo supplements will only be received for 10 days during the study.

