### Outcomes {12}

In general, the variables evaluated in this study will include demographic variables, assessment of disease severity, and evaluation of changes in sonographic findings of major salivary glands (including echogenicity, size, margin, and contour in sonography).

Demographic variables (including age, gender, marital status, smoking, medical history and medical history, education level, occupation, and use of supplements and drugs) will be collected from all participants by completing a general information questionnaire.

Before and 6 months after the 10-day intervention with selenium or placebo, sonography was taken from parotid and submandibular salivary glands and according to sonography, these salivary glands will be evaluated in terms of echogenicity, size, margin, and contour.

Huang et al.’s study including 446 patients with thyroid carcinoma, reported that the side effect of radioactive iodine on salivary glands occurs after a few months [40]. Also, Lee et al.’s study, which investigated the effect of selenium intake on reducing the side effects of radioactive iodine on salivary glands, examined the findings after 6 months [38]. Therefore, we will examine the changes in salivary gland sonographic findings after 6 months.

The level of taste sensation and secretion of salivary glands will be evaluated by the evaluation questionnaire of the level of sialadenitis [41]. This questionnaire contains 14 questions and each question can have between 1 and 4 scores (score 1, not at all; score 2, a few times; score 3, fairly often; and score 4, almost always.). Therefore, the overall score varies between 14 and 56 [41].

Before and 6 months after the 10-day intervention with selenium or placebo, 10 ml of blood will be taken from the patients and collected in plastic tubes. A centrifuge will be used to separate the serum samples. Then the serum will be poured into 0.5 ml microtubes. The samples will be stored in a freezer at − 70 °C. To reduce the error in the measurements, all blood samples will be taken at 8–10 am in the fasting state.

CRP will be evaluated at the beginning and end of the study, and if there will be no budget restrictions, we will also evaluate total antioxidant capacity (TAC) and superoxide dismutase (SOD).

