Another limitation is that due to a lack of funding, it is not possible to consider selenium blood biomarkers to assess adherence to supplements. To control this limitation, the patients will be closely monitored in such a way that the patients will be reminded daily by phone call to take the supplement during the ten days of the intervention. Also, patients return the empty can of the supplement after ten days. In addition, the potential benefits of the current research for patients are described in detail so that patients can cooperate better.

If the present study observes the effectiveness of selenium on thyroid cancer, selenium may be used as a safe supplement with a high potential in improving the symptoms of these patients in the near future.

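### Supplement use is restricted only before entry, while the retention message explains selenium's possible benefit to all patients; self-use before the single 6-month follow-up could blur the CRP comparison

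*Protocol article*

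**What the plan says.** - **Restriction on supplements.** The exclusion criteria {10} rule out patients who took any herbal, vitamin, mineral or other food supplement in the 3 months before entry. A separate criterion covers significant treatment changes, but only changes made by the doctor and only during the intervention period.
- **Concomitant care {11d}.** The section states "There will be no change in receiving standard care during the study", and describes the study capsules as the only addition to routine treatment. It gives no rule on supplements that patients obtain themselves.
- **Post-trial care {30}.** "selenium or placebo supplements will only be received for 10 days during the study".
- **Availability {6b}.** "the supplements available in the Iranian market have a dose of 200" µg per tablet, the same as the trial's daily dose.
- **Retention {18b}.** To secure cooperation, "it will be explained about the possible effects of selenium supplementation on the reduction of complications" due to radioiodine. The message is not limited to one arm. The limitations part of the Discussion adds that "the potential benefits of the current research for patients are described in detail so that patients can cooperate better".
- **Follow-up {18a}.** The salivary glands "will be examined by sonography before and 6 months after the 10-day intervention with selenium or placebo". Section {12} gives blood sampling the same two time points.
- **Detection.** The Discussion says that, for lack of funds, "it is not possible to consider selenium blood biomarkers to assess adherence to supplements". Section {12} lists "use of supplements and drugs" in the general information questionnaire, without a follow-up time point. The Discussion plans a review of drugs at the start and end of the study, with adjustment if the arms differ significantly; it does not name supplements.

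**The concern.** The protocol treats recent supplement use as serious enough to exclude a patient, and names herbal products, vitamins, minerals and omega-3. That protects the baseline. The same exposure is left unrestricted over the 6 months before the only outcome assessment, when it lies closest to the CRP sample. Meanwhile patients hear about selenium's possible benefit as a reason to stay in the trial, and selenium at the trial's daily dose can be bought locally.

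If placebo patients take selenium before the 6-month sample, the arms may move together on CRP. If patients in either arm take other supplements, CRP may become noisier. With no biomarker and no stated follow-up question, a null CRP result could not be told apart from one caused by outside use, and that information could not be reliably recovered later.

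**Working it through.** **1. Is the route open?** Setting the sections side by side:

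| Period | Rule on non-study supplements | Source |
|---|---|---|
| 3 months before entry | Use excludes the patient | Exclusion criteria {10} |
| 10-day course | None on self-use; only treatment changes by the doctor are covered | {10}, {11d} |
| End of course to 6 months | None | {11d}, {30} |

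The reminder calls ({11c} and Discussion) also cover only the ten days. The 6-month visit is therefore the one later contact that the article describes.

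**2. The plan's own figure.** Inputs from {14}: two-sided α = 0.05 (z = 1.96), 80% power (z = 0.84), SD 10.9, difference 8, with 1:1 allocation from {16a}.

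n per arm = 2 × (1.96 + 0.84)² × 10.9² / 8² = 2 × 7.84 × 118.81 / 64 = 29.11, rounded up to 30.

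This reproduces the stated 30 per arm. At 30 per arm, power = Φ[(8/10.9) × √15 − 1.96] = Φ(2.84 − 1.96) = 0.811 (0.798 with the exact t distribution). The formula contains no allowance for outside use.

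**3. Illustration for CRP only.** Assumptions, none of them in the protocol: a share c of placebo patients take selenium and obtain a fraction f of the full effect, nobody in the selenium arm gains anything extra, and the SD stays at 10.9. The expected difference becomes 8 × (1 − f·c), and power = Φ[2.84 × (1 − f·c) − 1.96].

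| c | Difference, f = 1 | Power, f = 1 | n per arm for 80%, f = 1 | Power, f = 0.5 |
|---|---|---|---|---|
| 0 | 8.0 | 0.811 | 30 | 0.811 |
| 10% | 7.2 | 0.725 | 36 | 0.770 |
| 20% | 6.4 | 0.623 | 46 | 0.725 |
| 30% | 5.6 | 0.512 | 60 | 0.676 |

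With the exact t distribution the f = 1 values are 0.711, 0.609 and 0.499 for c = 10%, 20% and 30%.

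**4. Use in both arms.** Suppose the same share c of selenium patients also self-supplement. If the extra intake acts equally in both arms, the difference stays at 8 − f·c·8 + f·c·8 = 8 and there is no dilution. If it adds nothing in patients already treated, the table applies unchanged. The truth may lie between these two cases.

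**5. Could the planned drug review repair it?** It names drugs, and adjusts only when the arms differ significantly. Blinded patients who hear the same message may self-supplement at similar rates in both arms, so no adjustment would follow even if placebo patients had taken selenium. Adjusting for use that began after randomisation would not restore the randomised contrast in any case.

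**The case against.** The strongest objection concerns timing. The experimental course is defined around radioiodine, from 3 days before to 6 days after. A reader might infer that a placebo patient who later buys ten days of 200 µg tablets (10 × 200 = 2,000 µg) has received the whole experimental course. The protocol does not support that: nothing in it says that selenium taken weeks or months afterwards reproduces an effect on the glands around radioiodine. This stands. The illustration should not be applied to the sonographic outcomes, which are the stated objective {7}, or to the sialadenitis questionnaire.

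A second objection is that the direction and size are hypothetical. No uptake rate is given, patients are blinded, and the message reaches both arms, so self-use may be balanced. This also stands, and it is why the figures are only illustrative. For the same reason, raised expectation on the self-reported questionnaire should be similar in both arms while blinding holds, and is not pressed here as a between-arm bias.

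Third, some text points the other way. Section {11d} describes the study capsules as the only addition to routine care, {30} confines supplements to 10 days, and {12} does collect supplement use. The first two describe what the trial supplies and do not bar a patient's own purchases. The third has no stated time point; because the timeline table is not shown, a repeat at 6 months cannot be ruled out.

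Fourth, the Discussion speaks of benefits of the research, not of selenium, so only {18b} clearly promotes selenium; and explaining possible effects is not the same as telling patients to take it. Both points are accepted. Consent also discloses the study's aims, but that does not require possible benefit to serve as the retention tool.

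Lastly, an article may leave detailed supplement rules and patient wording to the full protocol. That limits any complaint about brevity, but the retention message and the entry-only restriction are both stated in the text.

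**Conclusion.** The point holds as a moderate, inexpensive improvement. The protocol guards against supplement use before baseline but sets no limit over the 6 months before its only follow-up, and its stated retention message gives patients a possible reason to self-supplement. It shows an open route, not that crossover will occur.

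The main consequence is for CRP at 6 months, named as a primary outcome in {20a} and used for the sample size. Planned power of 0.81 would be about 0.73 or 0.62 if 10% or 20% of placebo patients alone obtained the full effect, and 0.77 or 0.725 with half the effect. There would be no loss if use were balanced and acted equally in both arms. These uptake and effect values are assumptions. For the gland outcomes the question stays open, because the protocol does not settle whether selenium taken after the radioiodine period still acts.

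**What to change.** 1. Reword the retention message in {18b}, and any matching explanation given under the Discussion's limitations, neutrally: it is not known whether selenium helps, and half of the patients receive placebo.
2. Carry the protocol's own entry restriction on non-prescribed supplements through to the 6-month assessment. State this in {11d} and at consent, and leave anything prescribed to the treating doctor.
3. Repeat the supplement question from {12} at the 6-month visit (product and duration), name supplements alongside drugs in the start-and-end review, and report use by arm.

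The cost is a change to protocol and patient-information wording and one question at a visit that is already planned. The downsides are a longer restriction for patients and possibly a slightly weaker motive to stay in the trial.

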### Data management {19}

The data will be carefully recorded and protected by a blind researcher. After completing the data, the result set will be reviewed.

### Confidentiality {27}

The ethical principles of confidentiality of the names and identification details of the patients will be fully maintained. The researchers will only mention the results of the study without mentioning the names and identification details of the patients, so the patients will not be identifiable under any circumstances.

### Plans for collection, laboratory evaluation, and storage of biological specimens for genetic or molecular analysis in this trial/future use {33}

After separating the serum from the collected blood samples, they will be immediately placed in a freezer at − 70°C until the tests will be performed. If the patient agrees, the blood sample will be stored for future studies. Genetic tests are not related to the present study.

## Statistical methods

### Statistical methods for primary and secondary outcomes {20a}

In this study, the number of quantitative variables will be reported as mean (standard deviation), and qualitative variables will be reported as number (percentage). The evaluation of the normality of the distribution of quantitative variables will be done using the skewness index and the Q-Q plot diagram. Intra-group analyses will be performed using paired *t*-test and between-group analyses will be performed using independent *t*-test and ANCOVA. The distribution of qualitative variables will be compared between two groups using the chi-square test. SPSS version 22 software will be used to analyze the data with a significance level of *P* < 0.05.

The primary results of this study include the evaluation of CRP and changes in sonographic findings of major salivary glands (including echogenicity, size, margin, and contour in sonography), and the secondary results include the evaluation of the level of taste sensation and secretion of salivary glands by the questionnaire to assess the level of sialadenitis [41].

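### The only test named for the categorical sonographic primaries is a plain chi-square, which makes no provision for baseline state, several glands per patient or the randomisation strata

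*Protocol article*

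**What the plan says.** All references are to the protocol article.

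- **Primary outcomes.** Statistical methods {20a}: "The primary results of this study include the evaluation of CRP and changes in sonographic findings of major salivary glands". The features listed are echogenicity, size, margin and contour.
- **Glands and times.** Outcomes {12} reports that "sonography was taken from parotid and submandibular salivary glands" and that "these salivary glands will be evaluated in terms of echogenicity, size, margin, and contour". It does not say whether left and right sides are scored separately. Plans for assessment {18a} confirms both time points: "Major salivary glands (echogenicity, size, margin, and contour) will be examined by sonography before and 6 months after the 10-day intervention with selenium or placebo".
- **Test for categorical data.** Statistical methods {20a}: "The distribution of qualitative variables will be compared between two groups using the chi-square test". No other between-arm method for categorical data is named.
- **Methods that can use baseline.** The same section: "Intra-group analyses will be performed using paired *t*-test and between-group analyses will be performed using independent *t*-test and ANCOVA". These suit quantitative outcomes such as CRP, the questionnaire score and gland size if it is measured.
- **Significance level.** "SPSS version 22 software will be used to analyze the data with a significance level of *P* < 0.05".
- **Randomisation.** Sequence generation {16a} stratifies by age (20 to 45, 46 to 65) and sex.

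The article does not say whether the unit of analysis is the gland or the patient, how several glands are combined, or whether the chi-square is applied to the 6-month state or to a change category.

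**The concern.** The named test does not fit the outcome as the same section defines it. The outcome is "changes in sonographic findings of major salivary glands", seen in at least two gland types per patient and measured twice. A chi-square compares one set of independent observations between two groups. It has no place for the baseline reading, for the likeness of glands within one mouth, or for the stratification factors. For quantitative outcomes the plan offers ANCOVA; for the categorical features it offers no equivalent, although the baseline scans will be available.

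Two different things are at stake, and they should be kept apart:

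1. **Precision.** Leaving out baseline wastes information in a trial of 30 per arm that was sized on CRP, not on sonography. It also leaves any chance imbalance in gland state uncorrected.
2. **Validity.** If each gland were entered as a separate observation, correlated readings would be counted as independent and the false-positive rate would rise. This depends on a choice of unit that the article leaves open.

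**Working it through.** **The plan's own figure.** Sample size {14} gives n = 2 × (1.96 + 0.84)² × 10.9² / 8² = 2 × 7.84 × 118.81 / 64 = 29.1, so 30 per arm and 60 in total. This reproduces; power at 30 per arm is 0.81. The figure concerns CRP and says nothing about power for sonography, but it fixes 30 patients per arm for what follows.

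**A. One value per patient.**

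*Level.* With one binary value per patient and 30 per arm, the simulated type I error of the chi-square is 0.050–0.051 (40,000 trials, event rates 0.3 and 0.5). When baseline abnormality of 0–40% is added and ignored, it is 0.046–0.053. The level holds.

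*Power.* Illustrative assumptions, not taken from the article: new abnormality by 6 months in 50% of one arm and 20% of the other among patients normal at baseline; patients abnormal at baseline remain abnormal.

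- With 20% abnormal at baseline, the 6-month proportions are 0.2 + 0.8 × 0.5 = 0.60 and 0.2 + 0.8 × 0.2 = 0.36. The contrast shrinks from 0.30 to 0.24.
- With 40% abnormal at baseline, they are 0.4 + 0.6 × 0.5 = 0.70 and 0.4 + 0.6 × 0.2 = 0.52. The contrast shrinks to 0.18.

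| Abnormal at baseline | Power, 6-month state | Power, new abnormality among those normal at baseline |
|---|---|---|
| 0% | 0.70 | 0.70 |
| 20% | 0.47 | 0.61 |
| 40% | 0.30 | 0.48 |

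The right-hand column is a simple stand-in for an analysis that uses baseline. Its simulated level is 0.051–0.054.

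**B. Glands pooled as independent units (conditional).**

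Inputs: m glands per patient, with m = 2 (two gland types) or m = 4 (if both sides are scored; an assumption). The intra-patient correlation (ICC) is not given and is assumed to lie between 0.2 and 0.8.

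Design effect: DE = 1 + (m − 1) × ICC. True type I error at nominal 5%: 2 × [1 − Φ(1.96 / √DE)].

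| m | ICC | DE | Type I, formula | Type I, beta-binomial simulation |
|---|---|---|---|---|
| 2 | 0.2 | 1.2 | 0.074 | 0.078 |
| 2 | 0.5 | 1.5 | 0.110 | 0.115–0.119 |
| 2 | 0.8 | 1.8 | 0.144 | 0.152–0.154 |
| 4 | 0.2 | 1.6 | 0.121 | 0.117–0.123 |
| 4 | 0.5 | 2.5 | 0.215 | 0.212–0.217 |
| 4 | 0.8 | 3.4 | 0.288 | 0.288–0.294 |

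With four glands, the apparent 120 observations per arm carry the information of 120/1.6 = 75, 120/2.5 = 48 or 120/3.4 ≈ 35 independent ones.

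**C. Sparse tables.** With 30 per arm, an expected count falls below 5 when fewer than 5/30 ≈ 17% of patients show a finding. The article gives no event rates, so whether this would happen is unknown. It bears on the choice of remedy.

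**The case against.** A reader might infer that the plan will overstate significance, or that its test cannot assess change. The text supports neither.

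- **Inflation is not the stated plan.** Nothing says that glands are the unit; Sample size {14} counts subjects. With one value per patient the test keeps its level. A separate test for each gland also keeps its level test by test; the number of tests is then a matter of multiplicity, not a fault of the chi-square. Four glands per patient is an assumption too.
- **Change could still be tested.** The article does not say that the chi-square is applied to the 6-month distribution. A chi-square on a per-patient category such as worsened or not worsened would test change and make some use of baseline.
- **Ignoring baseline is not a validity problem.** Under randomisation it costs power and leaves chance imbalance uncorrected; it does not inflate type I error.
- **Detail may sit elsewhere.** The article is condensed and an analysis plan may exist. The unit of analysis and a fallback for sparse tables are often fixed there.
- **Scope is inferred.** That echogenicity, margin and contour are categorical is reasonable but not stated. Gland size, if measured, is covered by ANCOVA.

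All of this stands, and it narrows the point. What remains is that the article does commit to a test for categorical data. No method it names for such data uses the baseline scan, the correlation within patients or the strata. That is a weakness in a stated choice, not a missing detail.

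**Conclusion.** The point holds in a limited form. For echogenicity, margin and contour, the one named test is poorly matched to an outcome defined as change and observed in several glands per patient. On a patient-level 6-month state the consequence is lost power: 0.47 against 0.61 with 20% abnormal at baseline and 0.30 against 0.48 with 40%, under assumed event rates and persistence of baseline abnormality. The type I error of about 7–14% (two glands) or 12–29% (four glands) is conditional on pooling glands as independent units and on an assumed ICC of 0.2–0.8. It is a risk left open by the wording, not something the plan prescribes. The change is worth making because a better-matched analysis is available from data already scheduled.

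**What to change.** For each listed categorical feature, replace the chi-square as the between-arm test with a logistic model (two categories) or an ordinal model (more than two) on arm, baseline state of the same feature, age stratum and sex. Fix one unit of analysis before unblinding:

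- **Patient level:** one value per patient, for example the worst gland, defined in the same way at baseline and 6 months; or
- **Gland level:** all glands, fitted by GEE clustered on patient with small-sample robust standard errors and each gland's own baseline state.

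State in advance what happens if the data are sparse: a penalised or exact method, or a per-patient comparison of worsened against not worsened. Keep each feature as its own outcome. A composite count of abnormal features would redefine the listed primaries and is not needed for this purpose.

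Cost: revised analysis wording and slightly more programming. With 60 patients and several covariates, the models may themselves run into sparse-data problems, which is why the fallback should be written down. No new data or visits are needed.

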### Objectives {7}

We aim to investigate the effects of selenium supplementation on sonographic findings of salivary glands in papillary thyroid cancer (PTC) patients treated with radioactive iodine. If this trial confirms our hypothesis, selenium supplementation may be used to improve the effects of existing treatments.

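### At least five unranked primary outcomes share one 5% significance level, and the objective, the sample size and the primary set do not match

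*Protocol article*

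**What the plan says.** Four places in the protocol article bear on which outcome decides the trial.

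- **Statistical methods for primary and secondary outcomes {20a}.** "The primary results of this study include the evaluation of CRP and changes in sonographic findings of major salivary glands", with the findings spelled out as "including echogenicity, size, margin, and contour in sonography". None of the five is put first. One level covers everything: "SPSS version 22 software will be used to analyze the data with a significance level of *P* < 0.05". For quantitative variables, "between-group analyses will be performed using independent *t*-test and ANCOVA", and neither test is named as the deciding one. Qualitative variables get a chi-square test.
- **Outcomes {12}.** "sonography was taken from parotid and submandibular salivary glands", and "these salivary glands will be evaluated in terms of echogenicity, size, margin, and contour". No per-patient summary across glands is described.
- **Objectives {7}.** "We aim to investigate the effects of selenium supplementation on sonographic findings of salivary glands". CRP is not mentioned. The Methods part of the abstract lists sonography, salivary secretion and taste, again without CRP.
- **Sample size {14}.** "we calculate the sample size base on CRP as one the most important parameters of this study". The calculation uses an SD of 10.9, a difference of 8, alpha 0.05 and 80% power, and arrives at 30 per group.

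**The concern.** Two problems meet here. First, five or more outcomes carry equal primary status at an unadjusted 0.05 each. The plan does not say which result, or how many, must be significant for the trial to count as positive. A report that treats any one significant primary result as a finding would then carry an error rate above the 5% that a reader assumes.

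Second, the question, the sizing and the primary analysis point to different endpoints. A trial positive on CRP alone would have a positive primary outcome that does not answer the stated objective. A trial positive on one sonographic feature would answer part of the objective with an outcome for which no power was calculated.

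**Working it through.** **1. The plan's own figure.** The inputs, all from Sample size {14}, are Z values 1.96 and 0.84, SD 10.9 and difference 8.

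n per arm = 2 × (1.96 + 0.84)² × 10.9² / 8² = 2 × 7.84 × 118.81 / 64 = 29.1, rounded up to 30.

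The stated 30 per group (60 in total) is reproduced. The standardised difference is 8/10.9 = 0.734. A two-sample t-test with 30 per arm then has 79.8% power at two-sided 0.05 (81.1% by the normal approximation). This is the power for CRP as a single test.

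**2. Number of primary tests.** One CRP outcome plus four sonographic features gives five, if each is tested once per patient. This is the only count that follows directly from section {20a}.

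**3. Chance of at least one false-positive primary result if selenium has no effect.** For k independent tests at 0.05 it is 1 − 0.95^k, so for k = 5 it is 1 − 0.95⁵ = 22.6%. The article gives no correlation between the outcomes, so a range is needed. The values for correlated tests come from simulating equicorrelated two-sided z-tests with 400,000 draws.

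| Pairwise correlation | Five tests |
|---|---|
| 0 | 22.6% |
| 0.3 | 20.9% |
| 0.5 | 18.2% |
| 0.8 | 12.8% |
| 0.9 | 10.1% |

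Across this range the error rate is about 2 to 4.5 times the nominal 5%.

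**4. If features were tested by gland (an assumption).** Four features in two gland types plus CRP is 4 × 2 + 1 = 9 tests. That gives 1 − 0.95⁹ = 37.0% if independent, 26.9% at correlation 0.5 and 12.3% at 0.9.

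**5. What control would cost at the planned size.** Holm over five outcomes tests the smallest p-value at 0.05/5 = 0.01. With 30 per arm and a standardised difference of 0.734, t-test power for CRP at 0.01 is 57.4% (60.5% by the normal approximation). Holm rejects CRP whenever its p-value is below 0.01, and may also reject it at a later, less strict step, so 57% is a lower bound. Restoring 80% power at 0.01 would take 44 per arm by the normal approximation, or 88 in total.

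**6. Alignment of the sections.**

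| Section | CRP | Sonographic features |
|---|---|---|
| Objectives {7} | not named | named |
| Sample size {14} | sole basis | no calculation |
| Primary results {20a} | primary | four features, all primary |

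No outcome appears in all three.

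**The case against.** The strongest reply is that multiplicity rules and the handling of several glands are often left to a statistical analysis plan or full protocol, and neither is shown. That stands as far as it goes: the lack of an adjustment method would be weak ground by itself. But this article does fix the list of primary outcomes, the single significance level, the objective and the endpoint used for sizing. A later document could add a multiplicity rule. It could not bring the objective, the sizing and the primary set into agreement without changing this text.

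A second reply is that sizing on CRP shows that CRP comes first. It does not: section {14} treats CRP as one of several important parameters, and section {20a} gives it no precedence.

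A third reply is that CRP belongs to the trial's purpose. This is fair. The Discussion notes that the earlier small trial did not examine inflammation or oxidative stress, and offers this as a reason for the present study. The objective is therefore better described as incomplete, and adding CRP to it is a legitimate repair.

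Three stronger readings are tempting, and the article does not support them:

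- A reader might infer that a false-positive primary result is likely. With five tests it is at most about 23% in the range examined, so no false positive remains the more probable outcome.
- A reader might count 9 tests, or 17 if left and right glands are separated (1 − 0.95¹⁷ = 58.2% if independent). No section says that features are tested per gland type or per side.
- A reader might infer that the plan lets any single significant test count as success. It states no success rule at all, so the figures above describe what happens if the results are read that way.

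**Conclusion.** The point holds. Section {20a} names at least five unranked primary outcomes at a flat 0.05. This puts the chance of at least one false-positive primary result at 22.6% under independence, falling to about 18% at correlation 0.5 and about 10% at 0.9. These figures assume one test per outcome, equal pairwise correlation and no effect of selenium. The 37% figure applies only under the added assumptions of testing by gland type and independence. Leaving open the choice between the t-test and ANCOVA adds some further flexibility, which was not quantified.

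Separately, and whatever the correlation, the objective (sonography only), the sample size (CRP only) and the primary set (both) do not match. The stated 80% power covers only CRP tested alone at 0.05. The sonographic primaries have no power statement.

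**What to change.** In section {20a}, take one of two routes:

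- name a single primary outcome; or
- keep the five, give each one patient-level between-group test (stating how glands are combined and which test decides), and apply Holm across the five or a fixed testing order. State that success requires a significant result under that procedure.

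Then align Objectives {7}, Sample size {14} and section {20a}, either by adding CRP to the objective or by making CRP secondary.

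Restate the power for what is chosen:

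- If CRP is the sole primary, or comes first in a fixed order, the existing calculation for CRP stands.
- Under Holm over five, report CRP power with 30 per arm as at least about 57%, or reconsider the sample size.
- If a sonographic outcome becomes the single primary, a new calculation is needed, because the article gives no SD or effect size for one.

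The cost is lower power per outcome under Holm, or a dependence on earlier results under a fixed order. The change also needs a protocol amendment with ethics committee approval and a registry update, as the article's section on protocol amendments {25} provides. No new data are needed. The change should be made before unblinding.
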